incidence of the malaria disease (uncomplicated and severe malaria). A cross-sectional survey will be carried after the third round in November/December to determine the coverage of SMC, the prevalence of the malaria parasitemia and anemia as well as humoral and cellular immune responses in a randomly selected number of children. Data collected in year 1 will be analyzed to determine the optimal delivery method (DDD+ DOT or DDD+NDOT or FPD+ DOT or FPD + NDOT) based primarily on the coverage of SMC and secondarily on the incidence of clinical malaria. The difference in SMC coverage is expected to be reflected in the incidence of clinical malaria, and the latter will be used to support the data on coverage of SMC. [Should there be no statistically significant difference between the arms in coverage and incidence of the disease, the easiest method of the delivery will be recommended for Year 2.](#)

In Year 2, SMC will be implemented using the optimal delivery system (determined in Year 1) in two sub-districts assigned during Year 2 after a census of children under 5 years of age. Villages in these two newly selected sub-districts will be randomized to receive either three or four SMC rounds during the transmission season starting in August. Baseline data on malaria parasitemia, markers of resistance to SP and AQ and immune responses to malaria antigens will be collected at baseline prior to the intervention in these two sub districts through a cross-sectional survey. In order to assess the effect of the fourth dose of SP and AQ, children will be followed passively to measure incidence rate of clinical malaria, and a cross-sectional survey will be carried out at the end of the malaria transmission season in November/December in a randomly selected sample of children to determine the prevalence of malaria infection, anemia, and humoral and cellular immune responses. Children that participated in Year 1 will continue to receive three rounds of SMC in Year 2 using the best delivery method identified in Year 1. The choice of the optimal number of doses will be based on the incidence of clinical malaria between the two arms of children in the two newly selected districts. An absolute difference of 7.5 episodes per 100 children per year will be considered meaningful.

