### ***Inclusion and exclusion criteria***

Children of either sex aged 3-59 months of age at the start of each period of drug administration will be eligible for inclusion in the trial, provided that parental consent is obtained. Children under the age of three months on the date of the start of drug administration will be excluded that year, as SMC is not recommended for children in this age group whose risk of acquiring malaria is low. Children who reach the age of 59 months or more at the end of the first or second years of treatment will not receive SMC in subsequent years. Exclusion criteria will be as limited as possible to make the results of the trial broadly applicable and will include i) a severe, chronic illness, ii) a known allergy to one of the study drugs, iii) known HIV positive subjects using Cotrimoxazole. [Children with acute clinical malaria at the time of SMC drug administration will be treated by ACT and will not be given SMC drugs during that round as per WHO recommendation. They will receive SMC drugs during subsequent cycles.](#)

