### ***Interventions***

SMC will consist of the administration of full treatment courses of sulfadoxine-pyrimethamine plus amodiaquine (SP+AQ) at monthly intervals during the peak of the malaria transmission season (August – through October or November depending on the year of the study and study arm). During each round, children aged 3–11 months will receive 75 mg of AQ given once daily

for 3 days plus a single dose of 250/12.5 mg of SP, while children aged 12–59 months will received 150 mg AQ base given once daily for 3 days and a single dose of 500/25 mg of SP. The single dose of SP will be given only on the first day, at the same time as the first dose of AQ. Children will be observed for 30 minutes after drug administration. If vomiting occurs during this period, drugs will be re-administered. If vomiting recurs this will be noted but the drugs will not be given on a third occasion. Such children will not be excluded from the trial and they will be eligible to receive drugs at the subsequent monthly treatment.

In villages assigned to door –to-door delivery (DDD), community health workers (CHW) will visit each compound to administer SMC drugs. In the villages assigned to fixed point distribution (FPD), children will receive SMC at a central fixed point in the village. The administration of the three days treatments at each round will be done by the CHW for children assigned to directly observed therapy (DOT) while for children assigned to non-directly observed therapy (NDOT), the treatment of first day will be given by the CHW and treatments for second and third days will be given by the caregiver at home for each round. SMC will be implemented using standardized field implementation guidelines developed by the WHO [WHO 2013] adapted to the situation in Mali. Monitoring and evaluation tools for SMC will be developed and integrated with the health system in Mali.

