### ***Subjects withdrawal criteria and handling***

Withdrawal criteria will include:

- Withdrawal of consent, HIV positive subjects under cotrimoxazole,
- Allergy or intolerance of SMC drugs and

- Travel outside the study villages.

For these subjects the administration of SMC drugs will be discontinued, but subjects will continue to receive routine health care services provided through the health centers in the areas.

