### **C. Final Analysis Plan**

*Describe statistical methods that will be used to analyze data.*

Data will be entered and verified using DataFax. The cleaned database will be exported to Stata (Houston Texas USA) or SAS for analysis. An intention-to-treat analysis will be used except for the immunological endpoints for which the exact number of the SMC treatments received will be considered.

SMC coverage will be determined using the information on the SMC card and from interview of parent or care giver and will be determined as the proportion of children who received all the treatments at all the SMC rounds during the transmission season. The proportion of children who received at least the first treatment dose of the SMC will be also estimated as secondary endpoints for SMC coverage. SMC coverage will be compared between arms and years of

interventions with 95% confidence intervals adjusted for cluster design (using cluster option in Stata for example). The DDD+NDOT arm will be considered as control group.

The census of the children will be updated at each round and at the end of the transmission season to allow a good estimation of person-time of follow-up. Cases of the clinical malaria will be recorded and the incidence rate of the clinical malaria defined as the number of clinical malaria episodes divided by total child days at risk. Children will not be considered at risk 21 days after a clinical malaria episode. Incidence rates of clinical malaria will be compared between treatment arms using generalized estimating equation to estimate the incidence rate ratio, with adjustment for age, previous SMC regimens and the lack of independence among repeated episodes in the same child.

Proportions of other secondary endpoints such as parasite prevalence, prevalence of anemia and frequency of molecular markers of resistance to SP and AQ and adverse events associated with study drugs will be estimated and compared between groups using generalized linear models with 95% confidence intervals, adjusted for cluster design and potential confounding variables such as age and use of ITN.

Differences at baseline will be compared using Chi-squared or Fisher's exact tests as appropriate for categorical variables and by analysis of the variances for quantitative variables that are normally distributed. Nonparametric tests will be used for non-normally distributed data.

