#### **4.11 Les critères de retrait des sujets et leur gestion**

Les critères de retrait seront les suivants :

- Retrait du consentement éclairé
- Sujets VIH positif sous prophylaxie au Cotrimoxazole
- Allergie ou intolérance à un des médicaments de la CPS
- Voyage hors des villages de l'étude. Pour ces sujets, l'administration de médicaments de la CPS sera interrompue, mais les sujets continueront à recevoir des services de soins de santé de routine à travers les centres de santé de la zone.

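### Travel is an unqualified ground for stopping SMC, with no limit to permanent departure and no rule for resuming on return

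*Protocol*

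**What the plan says.** The section on subject withdrawal (Protocol, section 4) gives "Travel outside the study villages" as a withdrawal criterion with no duration, no mention of permanence and no number of missed rounds. One handling rule covers every ground in the list: "For these subjects the administration of SMC drugs will be discontinued, but subjects will continue to receive routine health care services". Section 4.11 of the French text has the same unqualified criterion and consequence: "Voyage hors des villages de l'étude. Pour ces sujets, l'administration de médicaments de la CPS sera interrompue". Its verb is a little softer than the English, but it adds no rule for a child who comes back.

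Two other interruptions are handled differently. A child with acute malaria at a round is treated and skips that round, after which "They will receive SMC drugs during subsequent cycles" (Inclusion and exclusion criteria). For a child who vomits twice, "Such children will not be excluded from the trial and they will be eligible to receive drugs at the subsequent monthly treatment" (Interventions).

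Two statements set the Year 2 context. The choice between three and four rounds rests on the incidence of clinical malaria: "An absolute difference of 7.5 episodes per 100 children per year will be considered meaningful" (section 4.A, Overall design). On the analysis set, "An intention-to-treat analysis will be used except for the immunological endpoints" (section 5.C).

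**The concern.** The other grounds for stopping are refusal of consent or a reason of drug safety. Travel is neither. A child who has left for good cannot be dosed by the village health worker in any case, so an instruction to stop the drug has practical effect mainly on children who return. Those children would lose, during the transmission season, an intervention that the Background credits with cutting malaria by more than 80% in Malian children.

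The trial also has something at stake in Year 2. A four-round child who was away at round 2 or 3, was stopped, and is back for round 4 receives at most what a three-round child receives. Intention-to-treat keeps that child in the four-round arm, so the contrast shrinks toward no difference. The 5% allowance in section 5.A is for missing data and does not cover this. Villages that read the item differently would also handle the same situation differently.

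**Working it through.** **Text check.** Four places could supply a resumption rule for travel:
- *Inclusion and exclusion criteria*: eligibility is set by age and consent at the start of each period of drug administration. Travel is not an exclusion, but nothing here reverses a withdrawal.
- *Census and randomization*: the list is updated at each round and potentially eligible children are screened. The example is children newly reaching three months. Migration is recorded for person-time. Children withdrawn for travel are not mentioned.
- *Interventions*: continued eligibility is stated for vomiting only.
- *Quality Assurance*: standard operating procedures for the census and SMC administration are promised, with content not given.

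None overrides the withdrawal section. Taken literally, the rule has no exit.

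**Year 1.** Primary coverage requires every dose at all three rounds. A child who missed a round has already failed it, so refusing later rounds changes nothing. The rule could lower coverage only if a child who missed no dose were known to have travelled and were stopped, and no described procedure would detect that.

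**Year 2 illustration.** Inputs from section 5.A: rates of 0.3 and 0.225 per child per year, one-sided 0.025, 80% power, 1386 children per arm, 20 clusters per arm, intraclass correlation 0.01, 5% missing. Assumptions: the 0.075 difference holds when the rule stops nobody; a share s of the four-round arm misses round 4 only because of the rule; those children have the three-round rate; rounds lost before round 4 are equal in both arms.

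- Standard error implied by the plan: 0.075/(1.960 + 0.842) = 0.02677.
- Four-round rate: 0.225 + 0.075s. Difference: 0.075(1 − s).
- Standard error rescaled by √((0.3 + four-round rate)/0.525). Power = Φ(difference/SE − 1.960).

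| s | Children of 1386 | Difference per 100 | SE | Power |
|---|---|---|---|---|
| 0 | 0 | 7.50 | 0.02677 | 80% |
| 5% | about 69 | 7.1 | 0.02687 | Φ(0.69) = 75.6% |
| 10% | about 139 | 6.75 | 0.02696 | Φ(0.54) = 70.7% |

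For the expected observed difference to reach 7.5 per 100, the true effect of round 4 would have to be 7.5/0.95 = 7.9 or 7.5/0.90 = 8.3.

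**Sensitivity to the starting power.** With 1386 × 0.95 = 1317 children analysed, about 66 to 69 per cluster (after or before the missing-data allowance), Poisson variance and the usual design effect of 1.65 to 1.68:
- SE = √(0.525 × 1.65/1317) to √(0.525 × 1.68/1317) = 0.0256 to 0.0259, so undiluted power is about 82–83%.
- At s = 5% the same method gives about 78–79%.

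The starting point moves, but the loss is again about 4 points. The plan's quasi-Poisson overdispersion is not stated, so this is also an assumption.

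**How s might arise.** If a fraction m is absent at each round independently, and every child absent at round 2 or 3 is stopped, then s = (1 − (1 − m)²)(1 − m). Assumed m of 2%, 3% and 5% give s of 3.9%, 5.7% and 9.3%. This counts every absence at those rounds as travel and assumes that every village applies the strict reading, so for those absence rates it leans high. Absence at round 1 is left out.

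**The case against.** The strongest reply is that this is loose wording, not a wrong rule. Read to the letter, a day trip would end a child's SMC, which nobody can intend and nobody would detect. The surrounding text fits permanent departure: the census names migration and death as the exits it records, eligibility is reset at each period, and drugs are delivered from a regularly updated list. The promised operating procedures and the adapted WHO field guidance may settle what happens to a child absent at one round. Under that reading the effect is near zero. All of this stands as a limit on the consequence. It does not remove the point, because the written criterion is a positive instruction on dosing and an operating procedure should not have to reverse it.

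A reader might also infer that the protocol contradicts itself. It does not. The acute-malaria and vomiting rules concern children who are present at the round, and the aim that "Exclusion criteria will be as limited as possible to make the results of the trial broadly applicable" is about exclusion at entry, not withdrawal. The comparison shows that the protocol states resumption where it wants it, and no more.

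A reader might further infer that the Year 2 comparison is underpowered. The documents do not support that: no travel or absence rate is given, and every value of s above is assumed.

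**Conclusion.** The point holds as a minor one. Both language versions make unqualified travel a reason to stop SMC, and neither limits this to permanent departure or provides for return. The text does not settle which reading applies. If sites take it as permanent departure, the effect is near zero. If they apply it as written, returning children lose protection with no safety reason, and the Year 2 contrast is diluted by an amount that cannot be estimated from the protocol. The 5% case shows scale only: about 0.4 episodes per 100 children per year off the difference and about 4 percentage points off power, assuming that each affected child has the three-round rate. It is tempting to extend this to bias between the Year 1 delivery arms, but the all-rounds coverage definition gives no support for that, and none is claimed.

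**What to change.** In the withdrawal section of the English text and section 4.11 of the French text, replace the travel item with *permanent out-migration from the study villages*. Add one sentence: a temporarily absent child resumes SMC at the next round at which the child is present, and doses missed while absent count as not received, with the child analysed in the assigned arm.

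The cost is a wording change in two places. No new visits, data or analyses are needed, because the census update at each round already records migration.

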### **Quality Assurance/ Quality Control of Data and Collection**

An independent GCP monitor will be appointed by the sponsor (PEER-Health or NIAID/NH) to ensure that the study is conducted according to the study protocol, GCP, ethical and regulatory requirements standards are met. The monitor will conduct an initiation visit, a close out visit and at least one additional visit each year. S/he will examine a random selection of clinical and laboratory records during each visit.

SMC implementation tools will be developed in collaboration with the district health authorities. Standard operating procedures will be developed for each of the key activities including (consent, census, SMC administration, clinical exam, diagnosis and treatment of the malaria, sample collections and processing and lab techniques. Activities will be carried out by competent and trained staff. Initial training on the study protocol, GCP and GLP will be provided to the health staff in the intervention villages, as well additional staff of the project. Refresher training will be provided at least one year. Data will be collected in standardized forms. Quality control will be performed on sample of the RDTs in a routine manner and feedback and refresher training will be provided according to the procedures of the district health center. [SMC drugs will be sourced through reliable channels to ensure quality. SMC drugs, ACT for treatment of uncomplicated malaria, injectable quinine and artesunate for treatment of severe malaria, and RDT for malaria diagnosis will be provided by the USAID PMI as part of their support for SMC implementation and malaria control in Mali. Quality control of the drug will be performed by independent laboratory through USAID-PMI and CDC. Diagnosis and treatment for malaria in under -5 children is free in Mali.](#)

### **Patient Safety Considerations**

Risks to participants in the trial are small. The trial will use only licensed products and does not involve any new methods. Over 800,000 courses of SP and AQ have been given for SMC without any report of a drug associated severe adverse event (SAE) including when enhanced surveillance was used [Wilson et al 2011, Ndiaye et al . submitted]. Neither the less the serious adverse events will be monitored throughout the study period and any SAE related to the study

drugs will be reported to the Ethical Committee of the Faculty of Medicine, Pharmacy and Dentistry of the University of the Bamako and the within 24 hours the Principal Investigator has become aware of it.

*Definitions and Procedures for recording and reporting Adverse Events (AE) and Serious Adverse Events (SAE)*

An adverse event (AE) is defined as any clinical symptom or sign that occurs in study children after administration of the study drugs that may or may not have a causal relationship with the study drugs. A serious adverse event (SAE) is any clinical condition that fulfils at least one of the following criteria: results in death, is life-threatening (the child was at risk of death at the time of the adverse event), results in disability/incapacity. AE and SAE will be classified by severity, causality and outcome as described below

*Severity.* The severity of a clinical adverse event is to be scored according to the following scale:

- Mild: Awareness of sign or symptom, but easily tolerated.
- Moderate: Discomfort enough to cause interference with usual activity.
- Severe: Incapacitating with inability to perform usual activity.
- Life-threatening: Patients at risk of death at the time of the event.
- Death

*Assessment of Causality and Outcome.* The relationship between the study drugs and the occurrence of each AE/SAE will be determined based on their clinical judgment. Alternative causes, such as the natural history of the underlying diseases, concomitant therapy, other risk factors, and the temporal relationship of the event to the study drug will be considered and investigated. The relationship of an adverse event to study drug is to be assessed according to the following definitions:

- Definitely unrelated: events that had occurred prior to administration of the study drugs or events that are obviously unrelated to the study (e.g. accidental injury).
- Unlikely: There is no reasonable temporal association between the study drug and the suspected event and the event could have been produced by the child's clinical state or other concomitant medications.

- Possible: The suspected adverse event may or may not have a reasonable temporal association with the administration of study drug but the nature of the event is such that an association with the study drug cannot be ruled out. The event could be related to the child's clinical state or by concomitant medications.
- Probable: The suspected adverse event follows a reasonable temporal sequence after administration of study drugs, abates upon discontinuation of the drug, and cannot be reasonably explained by the known clinical state of the child.
- Definitely related: events that have no uncertainty in their association to the administration of study drugs.

*Outcome.* The outcome of each AE will be assessed according to the following classification:

- Completely recovered :           The child has fully recovered with no observable residual effects
- Not yet completely recovered :           the child's condition has improved, but still has some residual effects
- Deterioration :                   The child's overall condition has worsened
- Permanent damage :           The AE has resulted in a permanent impairment
- Death :                           The child died due to the AE
- Ongoing :                        The AE remains the same as at onset
- Unknown :                       The outcome of the AE is not known because of lost to follow-up

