## **5. Protection of Human Subjects/Ethical Considerations**

### **A. Ethical Standard**

The study will be conducted in compliance with the protocol, current Good Clinical Practice (GCP) guidelines, and all applicable regulatory requirements.

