### **6.5 Événements indésirables**

Les risques liés à la participation à l'étude sont mineurs. Dans cette étude, on utilisera uniquement des produits autorisés et on n'utilisera pas de nouvelles méthodes. Plus de 800 000 doses de traitement de SP et AQ ont été administrées dans le cadre de la CPS sans qu'aucun événement indésirable grave (EIG) soit associé au traitement, y compris lorsque la surveillance renforcée a été utilisée [8 ; 13]. Néanmoins les effets indésirables graves seront surveillés tout au long de la période d'étude et tout EIG lié aux médicaments de l'étude sera rapporté au Comité d'Ethique de la Faculté de Médecine, de Pharmacie et d'Odontostomatologie de l'Université des Sciences des Techniques et Technologie de Bamako dans les 48 heures après que l'investigateur principal aura été mis au courant.

*Définitions et procédures d'enregistrement et de déclaration des événements indésirables (EI) et les événements indésirables graves (EIG)*

Un événement indésirable (EI) est défini comme tout symptôme clinique ou un signe qui se produit chez les enfants de l'étude après l'administration des médicaments de l'étude qui peuvent ou peuvent ne pas avoir une relation de cause à effet avec les médicaments de l'étude. Un événement indésirable grave (EIG) est une condition clinique qui répond à au moins un des critères suivants : entraîner la mort, mettre en danger la vie (l'enfant était en danger de mort au moment de l'événement indésirable), provoque un handicap / incapacité. Les EI seront classés par ordre de gravité, la causalité et le devenir comme décrits ci-dessous. Gravité. La gravité d'un événement indésirable clinique doit être marquée selon le barème suivant :

- Léger: prise de conscience de signes ou symptômes, mais facilement tolérés.
- Modéré: assez pour causer des interférences avec l'activité habituelle, inconfort.
- Sévère : invalidant avec impossibilité d'exercer une activité habituelle.
- Menace le pronostic vital : Les patients à risque de mort au moment de l'événement.
- Décès

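### The SAE definition omits hospital admission, so an admitted drug reaction judged neither life-threatening nor disabling/incapacitating is handled as a non-serious AE with no expedited report

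*Protocol*

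**What the plan says.** The English text, under Patient Safety Considerations, states that an SAE "is any clinical condition that fulfils at least one of the following criteria", and then gives three: "results in death, is life-threatening (the child was at risk of death at the time of the adverse event), results in disability/incapacity". The French version, section 6.5, gives the same three: "entraîner la mort, mettre en danger la vie (l'enfant était en danger de mort au moment de l'événement indésirable), provoque un handicap / incapacité". No other part of the document shown adds a criterion.

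An AE is much broader: "any clinical symptom or sign that occurs in study children after administration of the study drugs", whether or not the drugs caused it. AEs are classified by severity, causality and outcome, and the Final Analysis Plan compares drug-associated AEs between groups.

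What goes to the ethics committee is "any SAE related to the study" drugs. The English text sets the time as "within 24 hours the Principal Investigator has become aware of it"; the French text sets it as "dans les 48 heures après que l'investigateur principal aura été mis au courant".

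Under Ethical Standard, the protocol commits to "current Good Clinical Practice (GCP) guidelines" but does not restate there what makes an event serious.

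**The concern.** The seriousness test decides which events leave the study team promptly. Two of its three criteria, death and threat to life, repeat the top two grades of the protocol's own severity scale, so the test adds only disability/incapacity to that scale. Admission to hospital, the most easily observed sign that a reaction was more than trivial, plays no part.

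At stake is prompt outside review of drug reactions in young children who receive repeated courses over up to three seasons. Allergy to the study drugs is a risk that the protocol itself names under Potential Risks. In the NDOT arms caregivers give the second and third days' treatment at home, so an admission may be how staff first learn of a reaction.

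**Working it through.** The point is one of definition. There is no planned figure to reproduce, so the check applies the written rule to a case and follows where the event goes.

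1. **Test case.** A child is admitted after SP+AQ with a reaction judged drug-related, is not at risk of death, and recovers without disability or incapacity.
2. **Is it an SAE?** Death: no. Threat to life: no. Disability/incapacity: no. The list is closed and at least one criterion must be met, so the event is not an SAE. The French list gives the same result, so this is not a translation slip.
3. **Is it an AE?** Yes. It is graded for severity and causality, and its outcome is recorded; complete recovery is one of the outcome categories. As a drug-associated AE it enters the group comparison in the Final Analysis Plan (French section 5.3).
4. **Does it reach the ethics committee promptly?** Not by any stated route. The expedited report is triggered only by a drug-related SAE.
5. **Does another stated review look at it before the final analysis?**
   - Planned Interim Analyses (French 5.2) cover SMC coverage, malaria incidence, parasite prevalence, immunological parameters and resistance markers, but not adverse events.
   - Study discontinuation (French 4.10) rests on drug resistance and on malaria incidence without SMC, but not on adverse events.
   - The independent monitor examines a random selection of records, with at least one visit a year besides the initiation and close-out visits.
6. **Is step 2 certain for every such child?** No. Incapacity is not defined and need not be lasting, and the Severe grade is described as incapacitating, with loss of usual activity. One assessor could count a severely ill admitted child under incapacity; another could reserve that term for lasting impairment.

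**Exposure** (ceiling of 10,800 children from Detailed Description of Study Population; three or four rounds; every child treated at every round in Year 3):
- 10,800 × 3 = 32,400 courses
- 10,800 × 4 = 43,200 courses

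These are upper limits on exposure, not counts of missed events. The documents give no rate of drug-related admission.

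**Added workload if admission becomes a criterion.** French section 4.1 puts severe malaria at about 1 to 2% of under-fives per transmission season in 2008. Assuming that rate, 10,800 children and admission of every case, before any SMC effect:
- 10,800 × 0.01 = 108 per season
- 10,800 × 0.02 = 216 per season

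Admissions for other causes would add to this; the documents give no figure for them.

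**Reporting times.** English 24 hours against French 48 hours, for the same report to the same committee. The two contradict each other.

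**The case against.** The strongest reply is that little is lost. The admitted child is still recorded, graded and analysed. The planned safety comparison is of drug-associated AEs, so the SAE label removes nothing from it; every randomised arm receives SP+AQ under the same definition, and no SAE outcome is listed among the primary or secondary outcomes. Other safeguards exist: 30 minutes' observation after dosing, exclusion for known allergy, discontinuation of SMC drugs for allergy or intolerance, and an independent monitor. Incapacity could be read widely enough to include many admitted children. Finally, no passage makes admission a seriousness criterion, so the omission is measured against general GCP practice and is not an internal contradiction.

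Most of this stands, and it rules out three stronger readings that a reader might infer:

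- *That such events are never reported.* They remain AEs and reach the final analysis; what is lost is SAE status and the expedited report.
- *That most non-fatal serious drug reactions are missed.* The documents give no rate, so no proportion can be claimed.
- *That the safety outcome is biased towards no drug-associated SAE.* The planned comparison does not depend on the SAE label. At most, a descriptive SAE count would be lower, and the document does not say what definition lay behind the 800,000 earlier courses it cites.

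What the reply does not remove is the gap in prompt reporting. The listed safeguards act on the individual child or on sampled records; none takes a drug-related admission promptly to a body outside the study team. A wide reading of incapacity is possible but not assured, and that uncertainty is itself a fault in the definition. The general commitment to GCP does not supply the missing criteria on the page that staff will apply.

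**Conclusion.** The point holds in a limited form. As written in both languages, a drug-related event that leads to admission but is judged neither life-threatening nor disabling/incapacitating is handled as a non-serious AE. It is kept in the data and in the final comparison, but it falls outside the only prompt external safety report that the protocol states.

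The number of children affected cannot be estimated from the documents. The undefined term incapacity makes classification depend on the assessor. The conflict between 24 and 48 hours is a separate, plain contradiction in the sentences governing the same report.

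This does not touch the primary outcomes. It is a safety-reporting weakness that is cheap to correct and should be corrected. The conclusion rests on the safety text as shown; nothing is inferred about the consent pages, which were removed.

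**What to change.** In Patient Safety Considerations and in French section 6.5:

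- add to the SAE criteria *requires or prolongs hospital admission* and *other medically important event*;
- state what incapacity means, in particular whether it must be lasting and how it relates to the Severe grade;
- word the two language versions identically, and carry the same text to the SAE form;
- reconcile the two reporting times.

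The drafting cost is a short amendment in each language and on the form. The running cost is more SAE forms and causality assessments, including those for severe malaria admissions estimated above and admissions for other causes. Expedited reports would rise far less than forms, because only drug-related SAEs go to the ethics committee. Severe malaria cases are already recorded through passive surveillance and can be cross-referenced.
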